#### 2.7.2. Secondary Outcome

The grades of oxaliplatin-induced peripheral neuropathy will be evaluated according to the grades of National Cancer Institute-Common Terminology Criteria for Adverse Events Version 5.0 (NCI-CTCAE 5.0, 0–5 grades, with higher grade meaning a worse outcome), which is evaluated by the doctor on 1 day before the oxaliplatin administration from cycle 1 to cycle 6, 1 month after the end of cycle 6, and then every 3 months up to 1 year.QOL will be evaluated according to the score of European Organization for Research and Treatment of Cancer's Core Quality of Life Questionnaire (EORTC QLQ-C30, 28–112 scores, with higher scores meaning a worse outcome) on 1 day before the oxaliplatin administration from cycle 1 to cycle 6, 1 month after the end of cycle 6, and then every 3 months up to 1 year.Chemotherapeutic efficacy will be evaluated according to Response Evaluation Criteria in Solid Tumors Version 1.1 (RECIST 1.1) at the end of cycle 3 (and cycle 6 if it exists).The number of completed chemotherapy cycles will be recorded at the end of cycle 6 or after the last chemotherapy. If the result is less then 6, the specific reason should be noted.

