## Abstract

*Background*. Oxaliplatin-induced peripheral neuropathy (OIPN) is one of the most common side effects of oxaliplatin, which can cause reduction and cessation of oxaliplatin-based chemotherapy and significantly affect patients' quality of life. However, no drug has got recognition to prevent or treat OIPN. Yiqi-Wenjing-Fang (YWF) is a joint name of Chinese medicine prescriptions with similar effects of tonifying qi and warming meridians, represented by Huangqi Guizhi Wuwu decoction (HGWD) and Danggui Sini decoction (DSD), both from “Treatise on Cold Pathogenic and Miscellaneous Diseases.” YWF granules, including HGWD granules and DSD granules, have been, respectively, demonstrated to be effective in preventing OIPN in previous small-sample observations. The purpose of this study is to enlarge the sample size for further evaluation of the preventive efficacy and safety of YWF granules on OIPN. *Methods and Analysis.* This study is a randomized, double-blind, placebo-controlled, and multicenter clinical trial. 360 postoperative patients with stage IIa-IIIc colorectal cancer will be randomly assigned into placebo-control group, intervention group I, and intervention group II, taking the mimetic granules of YWF as placebo, HGWD granules and DSD granules, respectively. All subjects will receive oxaliplatin-based chemotherapy regimen at the same time. EORTC QLQ-CIPN20 will be used to assess the degree of OIPN as the primary outcome measure. The grades of OIPN, quality of life, chemotherapeutic efficacy, and the number of completed chemotherapy cycles are selected as the secondary outcome measures. *Discussion*. Based on the condition of no recognized effective drugs in preventing OIPN, evidence-based medical study will be conducted for seeking a breakthrough in the field of Chinese herb medicine. This protocol could provide reliable and systemic research basis about the efficacy of YWF granules and the differentiation of two classical prescriptions of YWF on preventing OIPN objectively. *Trial Registration.* This study was registered at ClinicalTrials.gov on 26 December 2020 (ID: https://clinicaltrials.gov/ct2/show/NCT04690283).

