### 2.4. Sample Size Calculation

This study is suitable for superiority test. Although without positive-control group, the method of sample size calculation is equal to the three-arm trial. Based on the incidence of OIPN, the incidence of the placebo-control group was assumed as 40%, and the incidences of two intervention groups were both assumed as 20%. The Pearson chi-square test was used to calculate the appropriate sample size for each group. Taking the 20% shedding rate into account and rounding off, each group needs 120 samples and a total of 360 samples.

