#### 2.7.1. Primary Outcome

The degree of oxaliplatin-induced peripheral neuropathy will be evaluated according to the score of European Organization for Research and Treatment of Cancer Quality of Life Questionnaire-CIPN twenty-item scale (EORTC QLQ-CIPN20, 20–80 scores, with higher scores meaning a worse outcome), which is evaluated by the subject on 1 day before and 3 consecutive days after the first time of oxaliplatin administration. Subsequent assessments will be made every one time from cycle 2 to cycle 6, 1 month after the end of cycle 6, and then every 3 months up to 1 year.

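### The secondary quality-of-life outcome is fixed as one raw QLQ-C30 total of 28–112, which fits a sum of only 28 of the 30 items and weights every item equally

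*Protocol article*

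**What the plan says.** Quality of life is one of four secondary outcomes. The Abstract lists them: "The grades of OIPN, quality of life, chemotherapeutic efficacy, and the number of completed chemotherapy cycles are selected as the secondary outcome measures".

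Section 2.7.2 defines the outcome by one score: "QOL will be evaluated according to the score of European Organization for Research and Treatment of Cancer's Core Quality of Life Questionnaire". The range and direction follow in brackets: "EORTC QLQ-C30, 28–112 scores, with higher scores meaning a worse outcome". No subscale, transformation or second score is named. The questionnaire is completed the day before oxaliplatin in cycles 1 to 6, one month after cycle 6, and then every three months up to one year.

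Section 2.7.1 describes the primary instrument in the same style: "EORTC QLQ-CIPN20, 20–80 scores, with higher scores meaning a worse outcome". There the item count is spelled out: "Quality of Life Questionnaire-CIPN twenty-item scale".

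Section 2.10 says that a statistician will be engaged to write the analysis plan. It adds only that measurement data will be summarised as mean ± standard deviation and that counts or grades will be compared by chi-square.

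**The concern.** A range together with a direction is a scoring rule. The one given for the QLQ-C30 does not fit a 30-item questionnaire whose items are coded from 1, because the stated minimum of 28 is below 30. Someone who scores the data as section 2.7.2 says must leave two items out and add the others into one number.

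Two things are at stake. First, the only quality-of-life score in the protocol is silent on two items and does not say which they are. Second, an unweighted total lets movement in unrelated items mask, or be mistaken for, movement in the functions that neuropathy affects. Because the analysis plan is still to be written, its author inherits this definition. Using scale scores with different directions would then depart from the published outcome.

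**Working it through.** **Inputs**

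- CIPN20: 20 items, range 20–80, higher is worse (section 2.7.1).
- QLQ-C30: range 28–112, higher is worse (section 2.7.2).
- QLQ-C30 item count: 30, read from the instrument's name. The article does not state it separately.

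**Formula.** For a raw sum of *n* items, each coded from *a* to *b*, the range is *n* × *a* to *n* × *b*.

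**Step 1: reproduce the convention on the CIPN20.** With *n* = 20, *a* = 1, *b* = 4: 20 × 1 = 20 and 20 × 4 = 80. This matches the stated 20–80, so the article reports raw sums of items coded 1–4.

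**Step 2: apply it to the QLQ-C30.** With *n* = 28, *a* = 1, *b* = 4: 28 × 1 = 28 and 28 × 4 = 112. This matches the stated range exactly. A search over up to 30 equally coded items (lowest code 0 to 4, highest code up to 10) gave one other solution, 14 items coded 2–8. That is implausible and does not follow the CIPN20 convention.

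**Step 3: test a sum over all 30 items.**

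| Coding | Minimum | Maximum |
|---|---|---|
| Stated in 2.7.2 | 28 | 112 |
| 30 items coded 1–4 | 30 × 1 = 30 | 30 × 4 = 120 |
| 28 items coded 1–4 plus 2 items coded 1–7 (assumed) | 28 + 2 = 30 | 112 + 14 = 126 |

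Neither 30-item sum gives 28–112.

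**Step 4: size of the gap.** 30 − 28 = 2 items, or 2/30 = 6.7% of the questionnaire.

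**Step 5: which two items.** The article does not say. Suppose, as an assumption about the instrument, that they are the overall health and overall quality-of-life ratings, coded 1–7 with higher meaning better. That would explain both features of the text: a 1–7 code does not fit a sum of 1–4 codes, and an item on which higher is better cannot be added unreversed to a total on which higher is worse.

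**Step 6: weighting.** The total spans 112 − 28 = 84 points. A one-category change on any item moves it by 1/84 = 1.2% of that span, whatever the item measures. The article gives no standard deviation for the total, so the loss of sensitivity cannot be turned into a loss of power.

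**The case against.** The strongest reply is that this is a condensed article. The full protocol version cited in section 2.2 is not shown and the analysis plan is yet to come, and item-level scoring normally belongs there. The documents also give neither the content nor the coding of the QLQ-C30 items, so any statement about which two are missing comes from outside. Quality of life is secondary and plays no part in the sample size, which section 2.4 bases on neuropathy incidence of 40% versus 20%.

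The point about item content stands, and it is why the identity of the two items is carried here only as an assumption. The point about secondary status also stands and limits the weight of the finding. The appeal to the analysis plan does not succeed. Had section 2.7.2 merely named the questionnaire, its scoring could be left for later, but it commits to one total, one range and one direction.

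A reader might infer more than the documents support:

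- *That the score does not measure quality of life.* A sum of 28 items from a quality-of-life questionnaire still reflects health-related quality of life. What it lacks is two items and any separation of domains.
- *That two answers are collected and then thrown away.* The article does not say so. The full protocol or the analysis plan could score them separately, although the article names no such score.
- *That quality of life is a stated reason for the trial.* The Abstract gives the purpose as preventive efficacy and safety for neuropathy, and section 2.1 does not mention quality of life. Section 2.7 cites it only as a reason for repeated assessments.
- *That centres may sum all 30 answers and produce totals out of range.* Section 2.9 describes data entry, review and upload, and nowhere says that centres compute totals.
- *That the dilution has been quantified.* A one-category shift on three items would be 3/84 = 3.6% of the span, but both the shift and the number of items would be invented. Symptoms of chemotherapy arise in all randomised groups, so their main effect would be noise rather than bias.

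**Conclusion.** The point holds in limited form. Section 2.7.2 fixes the secondary quality-of-life outcome as a raw total whose range matches 28 items coded 1–4, two short of the 30 in the instrument's name, and merges those items with equal weight.

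The arithmetic rests on two premises: that the name gives the item count, and that the total follows the convention evident for the CIPN20. That the omitted items are the global ratings is a plausible assumption but is not established by the documents. The harm is a less complete and potentially less sensitive secondary outcome. No bias and no measurable power loss has been shown, and neither the primary outcome nor the planned 360 patients is affected. The change is still worth making before the analysis plan is written, because it costs so little.

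**What to change.** In section 2.7.2:

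1. Replace the raw 28–112 total with the instrument's own scale scores, and state the direction of each scale.
2. Score the two items now outside the total as their own scale, after checking their content and coding against the instrument's scoring manual.
3. Name one scale in advance as the main quality-of-life outcome, for example the global health/quality-of-life scale, with the other scales as supporting outcomes.

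Carry the same definition into the analysis plan. The cost is protocol wording and scoring code. The same questionnaire is completed at the same visits, no new data are needed, and the sample size of 360 does not change.

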### 2.3. Eligibility Criteria

#### 2.3.1. Inclusion Criteria

Subject diagnosed with stage IIa-IIIc colorectal cancer, confirmed by histopathological examination, according to Chinese Society of Clinical Oncology (CSCO) guidelines for diagnosis and treatment of colorectal cancer.Subject suitable for receiving FOLFOX4 or mFOLFOX6 or XELOX as adjuvant chemotherapy after radical resection of colorectal cancer, receiving each dose and cumulative dose of oxaliplatin of 85 mg/m^2^ and ≥540 mg/m^2^, respectively.Subject with Karnofsky Performance Status Scale (Schag et al. 1984) index ≥60 points and an expected survival time ≥6 months.Subject aged between 18 and 80 years, men or women.Subject without severe damage of the heart, liver, kidney, or hematopoietic system.

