#### 2.3.3. Termination Criteria

Subject withdraws from informed consent.Disease progression of subject is confirmed by imageological examination or clinical assessment.Subject experienced adverse events that the investigator deemed necessary to terminate trial treatment.Subject experienced severe side effects that the investigator deemed necessary to terminate trial treatment.Subject who stops or discontinues their medication without authorization.Subject who is less compliant with trial regulations intentionally or unintentionally.Other circumstances that may be detrimental to subject.

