## 3. Discussion

Oxaliplatin is a standard chemotherapy drug for colorectal cancer, and its toxic and side effects must be taken seriously. OIPN is the most common side effect which significantly affects the curative efficacy of chemotherapy and patients' quality of life and remains a refractory problem despite receiving extensive attention from researchers.

For seeking potential effective therapy, the pathogenesis of OIPN has been studied for a long time. Analysis of recent literature suggested that the alteration of voltage-gated Na^+^ channels, K^+^ channels, Ca^2+^ channels, and transient receptor potential (TRP) channels could be related to acute OIPN [2]. On the other hand, platinum accumulating in dorsal root ganglion so as to cause a series of neuronal damage, including nuclear DNA damage, mitochondrial dysfunction, oxidative stress, and axonopathy, is considered as the main mechanism of chronic OIPN [2, 35]. Regarding platinum accumulation, organic cation transporter 2 (OCT2) has been demonstrated to play an important role in platinum uptake and is expected to be a new target for prevention and treatment of OIPN [36, 37].

A number of agents have been proposed with potential therapeutic or preventive effects to OIPN. However, none of them have got recognition by further studies [1, 23]. Combining the theory of TCM, this study attributes OIPN to “arthromyodynia” [29]. YWF granules are a category of prescription granules with similar effects of tonifying qi and warming meridians, and they have been empirically used to treat arthromyodynia in China. In order to obtain scientific and precise evidence, several animal studies and randomized controlled clinical trials with small sample size have been conducted previously. Results showed that YWF granules can ameliorate OIPN syndrome without affecting the antitumor activity of oxaliplatin [30, 33]. Thus, we have designed the protocol for a randomized, placebo-controlled, double-blind, multicenter trial to enlarge the sample size for further evaluation of the preventive efficacy and safety of YWF granules. This study will provide objective evidence for the clinical application of YWF granules in preventing OIPN.

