21	Yangzhou Hospital of Traditional Chinese Medicine	Yangzhou, Jiangsu Province	[name]
22	Zhejiang Provincial Hospital of Chinese Medicine	Hangzhou, Zhejiang Province	[name]
23	Hangzhou Hospital of Traditional Chinese Medicine	Hangzhou, Zhejiang Province	[name]
24	The First Affiliated Hospital of Guangxi University of Chinese Medicine	Nanning, Guangxi Province	[name]
25	Henan Cancer Hospital	Zhengzhou, Henan Province	[name]
26	Affiliated Hospital of Traditional Chinese Medicine of Southwest Medical University	Luzhou, Sichuan Province	[name]
27	Affiliated Hospital of Shanxi University of Traditional Chinese Medicine	Xianyang, Shanxi Province	[name]
28	Hunan Academy of Traditional Chinese Medicine Affiliated Hospital	Changsha, Hunan Province	[name]
29	Hebei General Hospital	Shijiazhuang, Hebei Province	[name]
30	The First Affiliated Hospital of Guizhou University of Chinese Medicine	Guiyang, Guizhou Province	[name]

*Note*. Each center was randomly assigned the center number, and the ranking had nothing to do with the center scale and the number of planned enrollment.

**Table 2 tab2:** Chemotherapy regimen.

Abbreviated name	Components	Dosage	Mode of administration	Treatment course
FOLFOX4	Oxaliplatin	85 mg/m^2^	Intravenous infusion for >2 hours on day 1	Every 2 weeks, at least 3 cycles
	Leucovorin	200 mg/m^2^	Intravenous infusion for >2 hours on days 1 and 2	
	5-Fluorouracil	400 mg/m^2^	Intravenous injection on days 1 and 2	
		600 mg/m^2^	Continuous intravenous infusion for 22 hours on days 1 and 2	

mFOLFOX6	Oxaliplatin	85 mg/m^2^	Intravenous infusion for >2 hours on day 1	Every 2 weeks, at least 3 cycles
	Leucovorin	400 mg/m^2^	Intravenous infusion for >2 hours on day 1	
	5-Fluorouracil	400 mg/m^2^	Intravenous injection on day 1	
		1200 mg/m^2^	Continuous intravenous infusion for 22 hours on days 1 and 2	

XELOX	Oxaliplatin	130 mg/m^2^	Intravenous infusion for >2 hours on day 1	Every 3 weeks, at least 4 cycles
	Capecitabine	1000 mg/m^2^	Oral administration twice a day on days 1–14	

**Table 3 tab3:** Standard formulation of YWF granules.

Huangqi Guizhi Wuwu decocion (HGWD) granules			
Pinyin name	English name	Latin name	Doses, g
Huangqi	*Astragalus membranaceus*	Astragali Radix Membranacei	18
Guizhi	Cassia twig	Ramulus Cinnamomi	9
Baishao	Radix Paeoniae Alba	Paeoniae Radix Alba	9
Shengjiang	Ginger	Rhizoma Zingiberis Recens	9
Dazao	Jujube	Fructus Zizyphi Jujubae	9

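### RECIST 1.1 tumour response cannot be evaluated after radical resection, so the trial's only antitumour outcome says almost nothing about whether the granules preserve chemotherapy efficacy

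*Protocol article*

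**What the plan says.** **Population.** Section 2.3.1 of the protocol article requires "Subject diagnosed with stage IIa-IIIc colorectal cancer, confirmed by histopathological examination", and chemotherapy given "as adjuvant chemotherapy after radical resection of colorectal cancer". The Abstract agrees: "360 postoperative patients with stage IIa-IIIc colorectal cancer will be randomly assigned". No criterion asks for measurable or residual disease.

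**Outcome.** Section 2.7.2 states: "Chemotherapeutic efficacy will be evaluated according to Response Evaluation Criteria in Solid Tumors Version 1.1 (RECIST 1.1) at the end of cycle 3", with a second assessment after cycle 6 if that cycle is given. The Abstract confirms its status: "chemotherapeutic efficacy, and the number of completed chemotherapy cycles are selected as the secondary outcome measures".

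**Other tumour-related text.** No recurrence, disease-free survival or overall survival outcome is listed. Progression appears only in section 2.3.3, as a reason for termination: "Disease progression of subject is confirmed by imageological examination or clinical assessment". The Discussion reports from earlier studies that "YWF granules can ameliorate OIPN syndrome without affecting the antitumor activity of oxaliplatin", and the Introduction says much the same of the earlier HGWD trial.

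**The concern.** Response criteria grade the change in tumour that is present at baseline. These patients have had their tumour removed with radical intent. The outcome and the population do not fit each other, and an analysis plan could not repair that, because no choice of method creates a lesion to measure.

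The question behind the outcome matters. The granules are taken alongside adjuvant oxaliplatin, and the Introduction links HGWD to platinum transport and accumulation in the dorsal root ganglion. Whether a neuroprotective product leaves the antitumour effect intact is a natural benefit-risk question. RECIST is the only listed outcome that addresses it. The number of completed cycles shows how much chemotherapy was delivered, not what it did to the disease. If nearly every subject in every arm is recorded as free of disease, equal results would arise whether or not the granules weaken chemotherapy.

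**Working it through.** The plan gives no figure for this outcome, so there is nothing of its own to reproduce. The check sets eligibility against the outcome definition and then asks how much information remains.

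**1. Subjects with evaluable response.** Sections 2.3.1 and the Abstract: all 360 are postoperative, stage IIa-IIIc and radically resected. Expected number with a baseline target lesion: about 0 of 360. Response and disease-control rates have no valid denominator.

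**2. When the assessments fall.** Table 2 gives FOLFOX4 and mFOLFOX6 as "Every 2 weeks, at least 3 cycles", and XELOX in 3-week cycles.
- End of cycle 3: 3 × 2 = 6 weeks, or 3 × 3 = 9 weeks.
- End of cycle 6: 6 × 2 = 12 weeks, or 6 × 3 = 18 weeks.

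**3. What could still be recorded.** A new lesion could be logged as progression. The documents give no relapse rate. Assume 1% to 5% by these dates:
- per arm: 120 × 0.01 = 1.2 to 120 × 0.05 = 6 events;
- per pair of arms: 2.4 to 12 events.

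**4. What so few events can show.** Events needed to exclude a hazard ratio HR with 1:1 allocation, one-sided 0.025, 80% power and a true ratio of 1: 4 × (1.960 + 0.842)² / (ln HR)². Power with d events: Φ(√d / 2 × ln HR − 1.960). The margins are assumptions.

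| Margin (HR) | Events needed | Power with 12 events |
|---|---|---|
| 1.3 | 457 | 7% |
| 1.5 | 191 | 10% |
| 2.0 | 66 | 22% |

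Even the upper end of the assumed range cannot rule out a doubling of the relapse hazard.

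**5. Precision of a 1-year alternative.** For recurrence or death by 1 year, one active arm against placebo, with the same assumed rate p in both: half-width = 1.96 × √(2p(1 − p) / n). Section 2.4 gives n = 120 per arm and 20% dropout, so 120 × 0.8 = 96.

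| Assumed 1-year rate | n = 120 | n = 96 |
|---|---|---|
| 5% | ±5.5 points | ±6.2 points |
| 10% | ±7.6 points | ±8.5 points |
| 15% | ±9.0 points | ±10.1 points |

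The 96 column treats dropouts as lost to this outcome.

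**6. Limit of the alternative.** At 10% or 15%, a pair of arms yields 2 × 120 × 0.10 = 24 or 2 × 120 × 0.15 = 36 events. Power to exclude a hazard ratio of 1.5 by the formula in step 4 is then about 17% or 23%. The alternative describes tumour control; it cannot establish that efficacy is preserved.

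**The case against.** A reader might infer that the outcome cannot be measured at all. That goes too far. Response is not evaluable, but new lesions can be recorded at the two assessments, and section 2.3.3 would also bring confirmed progression to notice. What remains is a record of rare early relapse, too sparse to interpret.

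A reader might also infer that the trial sets out to prove preserved efficacy and fails in a main aim. The documents do not support this. Section 2.1 covers prevention of neuropathy and the comparison of HGWD with DSD. The statements on preserved efficacy in the Introduction and Discussion report earlier work. Nor does the article say that equal RECIST results will be presented as reassurance; that is a risk of misreading, not a stated analysis.

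A third objection concerns the remedy. A 1-year recurrence comparison is itself far too small to show preserved efficacy, so dropping the outcome is an equally valid answer. The work is also more than a change of wording. Section 2.8 lists CT and MRI for monitoring adverse events without a schedule. The visits up to 1 year serve CIPN20, CTCAE grades and QLQ-C30, not tumour surveillance. No section says that subjects who meet a termination criterion are followed for recurrence or death. Section 2.2 gives 18 months in all, so a full year of follow-up leaves at most about 6 months for enrolment, and less if the year runs from cycle 6.

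These objections narrow the point and raise the cost of the fix. They do not remove the mismatch between population and instrument.

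**Conclusion.** The point stands in limited form. By the trial's own eligibility criteria, RECIST response has no valid denominator, and what is left is a count of early relapses that cannot separate preserved from impaired efficacy. The first part follows from the text alone, reading radical resection as leaving no target lesion. The size of the second rests on the assumed 1% to 5% early relapse and on the assumed margins; the documents supply neither.

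It affects one secondary outcome. The primary CIPN20 outcome, the sample size and the randomisation are untouched. It should be fixed, because a named outcome is unsuited to the population and its likely result is easily misread, but the trial's main conclusion does not depend on it.

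**What to change.** Take one of two routes.

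- **Replace.** Define the outcome as recurrence or death (disease-free survival), recorded at the visits already planned up to 1 year, including for subjects who stop trial treatment. Report it by arm, with a 1-year difference or hazard ratio and 95% confidence interval for each active arm against placebo, and label it descriptive.
- **Drop.** Remove the RECIST outcome and draw no conclusion on antitumour efficacy from this trial.

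Under either route, state in the protocol that a non-significant comparison will not be reported as showing no effect on efficacy.

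Dropping costs only wording. Replacing needs eCRF fields for recurrence and vital status with dates, a rule for follow-up after termination, and a statement of how and when recurrence is ascertained, the same in all arms. The starting point of the 1-year follow-up should also be stated and checked against the 18-month duration. The price is an imprecise comparison that must be presented as such.
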